### Relevant Concomitant Care Permitted or Prohibited During the Trial

In line with standard practice, participants will be discouraged from bearing weight on the ulcer site, since weight bearing and the patients’ level of activity might affect the ulcer’s rate of healing. Participants will be asked to wear pedometers on the nonaffected foot, and the level of activity will be recorded on the tablet at each dressing change from the first dressing change until 84 days from randomization or discharge, whichever comes first.

### Provisions for Posttrial Care

The date of discharge will be noted, along with participant contact details, addresses, and contact details for at least 1 family member. The participants will be routinely contacted 6 months after randomization. The treated ulcer area will be examined and photographed. The researcher will take photographs of the ulcer area (healed in the majority of cases). The dates covering any readmissions to any hospital for the treatment of the “trial ulcer” will be recorded.

### Outcomes

We define 2 main outcomes relating to ulcer healing. The main outcomes will be (1) rate of healing based on 2 observations per week (until healed or 84 d from randomization) and (2) time to healing defined as complete re-epithelization (up to 84 d). Secondary outcomes will be (1) the recurrence of treated ulcer and (2) appearance of a new ulcer. Long-term outcomes will be measured at the follow-up 6 months after randomization, which will be (1) the number of days hospitalized prior to discharge and in total (to include any readmission related to leprosy ulcers) by 6 months and (2) the number of visits to any health care facility from discharge to the end of follow-up at 6 months.

### Participant Timeline

Participants’ timeline through the trial is outlined in Figure 2.

**Figure 2. F2:**
[figure not shown]
Timeline (in months) for the Honey Experiment on Leprosy Ulcer (HELP) trial (based on the most pessimistic estimate).

### Sample Size

Recruitment will continue for 24 months. We expect to enroll between 90 and 130 participants. Sample size was based on the 2 clinical outcomes: the rate of healing and time to complete re-epithelialization. We expect at least 70% of ulcers to heal within 84 days with standard care (according to a recent study of neuropathic ulcers, with over half due to leprosy [16]). If we assume that the intervention will increase this proportion to 90% and hazards are constant and proportional (so that the hazard ratio is 1.91 for discharge), for a 2-sided test of the hazard ratio with a type I error of 5%, a statistical power of 80%, and a 1:1 allocation ratio, 47 individuals are required in each group. With 130 participants, this allows for a dropout rate of up to 40% to achieve a power of 80%. At the most pessimistic sample size of 90, with a dropout rate of 40%, our minimum detectable effect size (ie, the effect size that achieves a power of 80% with 33 patients per arm) is a hazard ratio of 2.15, or 92.5% of patients in the treatment group being discharged by the end of the trial period. At the most optimistic sample size of 130 with no dropout, our minimum detectable effect size is a hazard ratio of 1.74, or 87.3% of patients being discharged in the treatment group. All calculations are based on a log-rank test.

We took a conservative approach and based the sample size calculation on the healing outcome and model with lower efficiency to ensure an adequate sample size for all main outcomes, since our inferential approach is not based on statistical significance but on a consideration of effect sizes and a comparison and triangulation of the totality of evidence. We are not particularly concerned with being “overpowered” or with a problem of multiple comparisons; instead, we will focus on ensuring a sufficient sample size to estimate clinical effectiveness to a reasonable degree of precision [17,18].

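### The 40% dropout figures do not follow from the plan's own sample size: 130 participants tolerate about 27% dropout, and 90 with 40% dropout leave 27 per arm, not 33

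*Protocol article*

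**What the plan says.** All of the figures are in the Sample Size section of the protocol article.

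- **Control arm:** "We expect at least 70% of ulcers to heal within 84 days with standard care".
- **Target effect:** the plan supposes that "the intervention will increase this proportion to 90% and hazards are constant and proportional (so that the hazard ratio is 1.91 for discharge").
- **Error rates:** the calculation is "for a 2-sided test of the hazard ratio with a type I error of 5%, a statistical power of 80%, and a 1:1 allocation ratio", and the section says that it uses a log-rank test throughout.
- **Requirement:** "47 individuals are required in each group".
- **Dropout tolerance:** "With 130 participants, this allows for a dropout rate of up to 40% to achieve a power of 80"%.
- **Pessimistic case:** "At the most pessimistic sample size of 90, with a dropout rate of 40%, our minimum detectable effect size" is described as "the effect size that achieves a power of 80% with 33 patients per arm" and is given as a hazard ratio of 2.15, or 92.5% in the treatment group.
- **Optimistic case:** 130 with no dropout gives a hazard ratio of 1.74, or "87.3% of patients being discharged in the treatment group".

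**The concern.** The tolerance statement and the requirement just before it cannot both be right: 60% of 130 is 78, which is 16 short of 94. The pessimistic case fails in the same direction, since 60% of 90 is 54, while 33 per arm is 66.

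The enrolment range of 90 to 130, the attrition the trial claims to withstand and the effect it claims to detect in its worst case all pass through this step. The 40% figure is also the only benchmark in the article for how much loss is acceptable. If the trial lost 30–40% of its participants and found no clear difference, readers would take the result as coming from a trial that still had 80% power for a hazard ratio of 1.91. By the plan's own method it would not have had it.

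**Working it through.** **Inputs (all from Sample Size).** Healing by day 84 of 70% and 90%; constant proportional hazards; two-sided 5% error; 80% power; 1:1 allocation; log-rank test; 130 or 90 enrolled; 40% dropout.

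**Step 1. Reproduce the base figure.**
- Hazard ratio = ln(0.10)/ln(0.30) = 1.912. The plan says 1.91.
- Events (Schoenfeld) = 4(1.96 + 0.8416)² / (ln 1.912)² = 74.7.
- Mean event probability = (0.70 + 0.90)/2 = 0.80, so total n = 74.7/0.80 = 93.3, or 47 per group. This agrees with the plan.
- Freedman's formula gives 80 events and 50 per group, so the plan evidently used Schoenfeld.

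**Step 2. Reproduce the stated detectable effects for the stated arm sizes.** For n per arm, solve n × (0.70 + 1 − 0.3^HR) = 4(1.96 + 0.8416)² / (ln HR)².
- 33 per arm: HR 2.149, 92.5%. This agrees.
- 65 per arm: HR 1.739. The hazard ratio agrees, but 1 − 0.3^1.74 = 87.7%, not 87.3%. Rounding does not explain the gap, because HR 1.735 to 1.745 gives 87.6% to 87.8%.

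The formula is therefore recovered. What remains is the step from enrolled to evaluable participants.

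**Step 3. The dropout step.** Evaluable = enrolled × (1 − d).

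| Enrolled | Dropout | Evaluable | Per arm | Plan implies |
|---|---|---|---|---|
| 130 | 40% | 130 × 0.6 = 78 | 39 | 47 |
| 90 | 40% | 90 × 0.6 = 54 | 27 | 33 |

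- Largest dropout at 130 that leaves 94: 1 − 94/130 = 27.7%.
- Enrolment needed to leave 94 after 40% dropout: 94/0.6 = 156.7, so 157.
- Dropout that takes 90 down to 66: 1 − 66/90 = 26.7%.

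The stated pairs roughly fit multiplying by (1 + d) where dividing by (1 − d) was needed: 94 × 1.4 = 131.6 and 66 × 1.4 = 92.4. That is an inference about the cause, and the finding does not depend on it.

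**Step 4. Consequences under the plan's method.** Power = Φ(√events × ln(HR)/2 − 1.96). At HR 1.912, events = 0.80 × evaluable participants.

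| Scenario | Per arm | Events | Power at HR 1.91 |
|---|---|---|---|
| The plan's requirement | 47 | 75.2 | 80.3% |
| 130, 40% dropout | 39 | 62.4 | 72.6% |
| 90, 40% dropout | 27 | 43.2 | 56.8% |

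At 27 per arm the minimum detectable hazard ratio is 2.32, or 1 − 0.3^2.32 = 93.9% healed. Power at the stated hazard ratio of 2.15 with 27 per arm is 71.7%. Freedman's formula is less favourable in both cases: 69.7% power at 39 per arm, and a detectable hazard ratio of 2.45 at 27 per arm.

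**The case against.** **The percentage may be wrong, not the arm sizes.** The retention fractions implied by the two statements nearly agree: 94/130 = 72.3% and 66/90 = 73.3%. If the intended dropout was about 27%, then 33 per arm, 2.15 and 92.5% all stand and only the label 40% is wrong, twice. This is a fair point about the repair, and only the authors can say what they meant. Either way, the statements as printed at 40% are false.

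**Dropouts are not lost altogether.** The Statistical Methods section plans a Cox model with right censoring, so a participant who leaves early still contributes time, and possibly an event, up to that point. Assuming exponential dropout and 130 enrolled, power at HR 1.91 is about 86% if 40% is the marginal probability of dropping out by day 84. It is about 78% if 40% are actually seen to drop out before healing or day 84. So 73% is the figure when dropouts contribute nothing, and the true loss of power could be smaller. But this is not the calculation in the plan, which removes dropouts to reach a count per arm. The first censoring model also gives a detectable hazard ratio of about 2.05 at 90 enrolled, so it does not recover 33 per arm or 2.15.

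**Inference does not rest on significance.** The section says so, and no analysis depends on the dropout percentage. Yet the plan states power and detectable effects, adjusts P values for multiplicity and sets a significance threshold at the interim analysis. Having given these figures, it should give them correctly.

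**Conclusion.** The concern holds. The requirement of 47 per group is right, as is the hazard ratio of 2.15 for 33 per arm and of 1.74 for 65 per arm. What fails is the link from enrolment with 40% dropout to those arm sizes.

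At 130 enrolled, the tolerable dropout is 12 percentage points lower than stated (27.7% against 40%), and power at 40% is about 7 points below the claimed 80%. At 90 enrolled with 40% dropout, each arm is 6 participants smaller than stated and the detectable hazard ratio moves from 2.15 to 2.32.

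These sizes rest on the plan's own assumptions: 70% control healing, constant proportional hazards, Schoenfeld's formula, and dropouts contributing no information. The arithmetic contradiction rests on none of them. The 87.3% is a separate slip of 0.4 points with no practical consequence.

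**What to change.** Replace the dropout statements in Sample Size with text such as: *130 participants allow up to 27% dropout for 80% power at a hazard ratio of 1.91; at 40% dropout (39 per arm) power is about 73%. With 90 participants and 40% dropout (27 per arm), the minimum detectable effect is a hazard ratio of 2.32, or 93.9% healed.* Correct 87.3% to 87.7%.

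If the authors meant about 27% dropout in the pessimistic case, they can keep 33 per arm, 2.15 and 92.5% and change the percentage there instead. In either form, add that these figures count dropouts as contributing no follow-up. If partial follow-up was meant to count, the dropout model should be stated and every figure recalculated under it.

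The cost is wording only. No participants are added, and treatment, conduct and analysis are unchanged. The price is that the stated robustness to attrition becomes less favourable. Keeping 80% power at 40% dropout by enrolment alone would need 157 participants, above the planned ceiling of 130.

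### Sample size: the best-case minimum detectable hazard ratio of 1.74 corresponds to 87.7% in the honey arm, not the printed 87.3%

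*Protocol article*

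**What the plan says.** The Sample Size section of the protocol article sets the control rate first: "We expect at least 70% of ulcers to heal within 84 days with standard care". It then posits 90% with honey and states that "hazards are constant and proportional (so that the hazard ratio is 1.91 for discharge". At a two-sided 5% level it concludes: "a statistical power of 80%, and a 1:1 allocation ratio, 47 individuals are required in each group". The section says that all its calculations use a log-rank test.

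Two further scenarios give minimum detectable effects at 80% power. With 33 per arm the effect "is a hazard ratio of 2.15, or 92.5% of patients in the treatment group being discharged by the end of the trial period". With the full 130 and no losses: "our minimum detectable effect size is a hazard ratio of 1.74, or 87.3% of patients being discharged in the treatment group".

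Each scenario pairs a hazard ratio with a honey-arm proportion. The section moves from healing to discharge between sentences but treats them as the same event, since it attaches the 1.91 derived from healing percentages to discharge. The same reading is used here.

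**The concern.** Once the control proportion is fixed at 70% and hazards are proportional, the hazard ratio and the honey-arm proportion determine each other. The last pair breaks that link, so at least one of its two figures is wrong.

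The sentence states the smallest effect that the trial can detect with 80% power at full enrolment. Clinical readers are likely to take the percentage rather than the hazard ratio, and the section itself says that inference will rest on effect sizes. If the percentage is the wrong figure, it credits the trial with 80% power for an effect slightly smaller than the one it can detect.

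**Working it through.** **Inputs, all from the Sample Size section:** control proportion 0.70 at day 84; constant, proportional hazards; two-sided 5% level; 80% power; 1:1 allocation; log-rank test; 130 participants without dropout, which is 65 per arm.

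**1. Conversion.** Under proportional hazards the proportion still unhealed in the honey arm is the control proportion raised to the power HR:

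p = 1 − 0.30^HR, and in reverse HR = ln(1 − p) / ln(0.30).

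| Printed HR | 1 − 0.30^HR | Printed % | HR implied by printed % |
|---|---|---|---|
| 1.91 | 90.0% | 90% | 1.912 |
| 2.15 | 92.5% | 92.5% | 2.151 |
| 1.74 | **87.7%** | **87.3%** | **1.714** |

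Two pairs agree to the printed precision and the third does not.

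**2. Rounding.** Hazard ratios that round to 1.74 (1.735 to 1.745) give 87.6% to 87.8%. Proportions that round to 87.3% (87.25% to 87.35%) give hazard ratios of 1.711 to 1.717, which would be printed as 1.71 or 1.72. The two ranges do not meet.

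**3. Which figure is wrong.** Schoenfeld's formula for required events is

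D = 4 × (1.960 + 0.842)² / (ln HR)² = 31.4 / (ln HR)²,

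with n per arm = D / (0.70 + p).

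The plan's own base case comes first. For HR 1.91, D = 31.4 / 0.647² = 75 events, and 75 / (0.70 + 0.90) = 46.9, so 47 per arm as printed.

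Solving the same formula for the hazard ratio that has 80% power:

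| n per arm | HR | p | Printed |
|---|---|---|---|
| 47 | 1.908 | 90.0% | 1.91, 90% |
| 33 | 2.149 | 92.5% | 2.15, 92.5% |
| 65 | 1.739 | 87.7% | 1.74, 87.3% |

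Every printed number is reproduced except 87.3%. The hazard ratio of 1.74 is right for 65 per arm, and the percentage is the error.

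**4. Power at 65 per arm.** Power = Φ(√(D/4) × ln HR − 1.960), with D = 65 × (0.70 + p).

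- HR 1.74, p = 0.877: D = 102.5; √25.62 × 0.554 − 1.960 = 0.844; power 80.1%.
- p = 0.873, HR 1.714: D = 65 × 1.573 = 102.2; √25.56 × 0.539 − 1.960 = 0.764; power 77.8%.

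A log-rank simulation (40,000 runs, exponential healing times censored at day 84) gives 80.2% and 77.4%.

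For 80% power at 87.3%, D = 31.4 / 0.539² ≈ 108 and 108 / 1.573 ≈ 69 per arm. That is 138 participants, above the maximum of 130.

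**5. Other explanations tried.** Freedman's formula gives a minimum detectable hazard ratio of 1.764, or 88.0%, at 65 per arm, which is further from 87.3%. A control rate of 69.5%, which would round to 70%, does pair 1.74 with 87.3%. But it turns 90% into a hazard ratio of ln(0.10) / ln(0.305) = 1.94, against the printed 1.91, so it breaks a pair that now agrees.

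**The case against.** The arithmetic is hard to dispute; the objections concern weight.

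- **The stated sensitivity is right on the scale that is powered.** The test is of the hazard ratio, the sentence leads with 1.74, and that figure is correct. The 77.8% arises only if the reader sets the hazard ratio aside and takes the percentage. This is fair, and it is why the point amounts to a wrong conversion beside a correct hazard ratio. But the sentence offers the percentage as an equivalent, and as an equivalent it is wrong.
- **The gap is within the looseness of the method.** Moving from Schoenfeld to Freedman lowers power at HR 1.74 from 80.1% to 78.1%, about the same shift, and the control rate is given only as a lower bound. This bears on how much the slip matters. It does not make the two printed figures agree under the section's own assumptions.
- **Nothing depends on the number.** This stands. The 47 per arm, the recruitment range and the interim trigger of 49 participants do not use 87.3%.
- **The same section has larger problems.** Also true: 40% dropout from 90 leaves 90 × 0.6 / 2 = 27 per arm, not 33, and from 130 it leaves 130 × 0.6 / 2 = 39, below 47. That is a separate matter, because the scenario at issue here has no dropout.

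**Conclusion.** The point holds as a minor error: the percentage is wrong as written. Under the section's own assumptions (70% in the control arm, proportional hazards, discharge standing for healing), a hazard ratio of 1.74 means 87.7% in the honey arm. The printed value is 0.4 percentage points too favourable, and the power attached to it is 77.8% rather than 80%, about 2 points lower.

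The mismatch itself needs only the conversion rule. Naming the percentage as the wrong half rests on the Schoenfeld formula, which is well supported because it returns every other figure in these scenarios. No design or analysis decision changes.

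**What to change.** In the last scenario of the Sample Size section, replace 87.3% with 87.7% and keep the hazard ratio of 1.74. The best case then reads as 70% against 87.7%, with 80% power at 65 per arm.

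The cost is one number in the text, and the stated effect becomes slightly less favourable. It can be corrected together with the dropout figures in the same section.

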### Recruitment

Eligible individuals are identified by the on-site clinical research team and are invited to take part in the study.

### Assignment of Interventions: Allocation

#### Sequence Generation

Participants will be enrolled sequentially, stratified by ulcer size (above or below 10 cm^2^) and randomly allocated (1:1) to undergo honey treatment or usual care with normal saline using a “digital sealed envelope” method [19].

#### Concealment Mechanism

An allocation table will be generated remotely at the trials office at The University of Ibadan. A permuted block randomization method will be used to generate the randomization sequence within each stratum. Randomly selecting blocks of size 2, 4, 6, or 8 will be generated in order to maintain balance between the numbers allocated to each of the 2 groups and to ensure allocation concealment. The generated table will be uploaded into the REDCap database platform to be used for participant enrollment. Access to the allocation table will be restricted. Trial staff in Nigeria will not have access to the allocation table. When a participant’s details are submitted, the trial arm and a unique study number will be assigned and revealed to the local clinician so that the randomized group that the participant is assigned to cannot be altered.

#### Implementation

A trial statistician at The University of Ibadan will generate the allocation sequence while researchers and clinical staff on-site will enroll and assign participants to the respective control or intervention groups.

### Assignment of Interventions: Blinding

#### Researcher Blinding

Only the overall on-site research supervisor, the database managers at the University of Birmingham and the University of Ibadan Trials Unit, the clinical staff carrying out dressing changes in the room designated for this purpose, and the participants themselves will be aware of the participants’ randomly assigned group. Ward staff will not be informed. The assessors in Nepal will be blinded from the treatment provided for the randomly assigned groups.

#### Procedure for Unblinding if Needed

There is no provision for the unblinding of trial participants during the trial.

### Data Collection and Management

#### Plans for the Assessment and Collection of Outcomes

Standardized photographs [20] will be taken twice weekly of the dressing changes during the in-patient stay for participants in both intervention and control groups. Any residual honey will be gently removed with a wet swab. Photographs will be taken using the built-in camera in the tablet devices (Samsung Galaxy Tab S7, 13Mp). The photographs will be taken perpendicular to the ulcer. For calibration purposes, a 3-cm clean paper ruler with the date and participant’s trial identification number will be placed in the photograph frame above or below the ulcer but at the level of the skin. The photographs will then be uploaded onto the REDCap database platform and accessed by database managers at the University of Birmingham. The ulcer photos will then be randomized and sent to the blinded assessors in Nepal for the measurement of ulcer dimensions. The photographs will be evaluated digitally by the designated observer in Nepal using the PictZar Digital Planimetry Software with the electronic PUSH Tool (National Pressure Injury Advisory Panel [21]). The observer will delineate an area of interest by manually “painting” the ulcer area with color using a computer mouse. The software will then calculate the ulcer dimensions based on this profile.

The assessors will be blinded to the treatment allocated to the participant. The assessors are all experienced in leprosy, ulcer care, and the measurement of ulcers using the PictZar software. All photographs from a given participant will be assigned to the observers at random. To ensure that the measurements are not all relegated to the end of the study, they will be made in batches of 10 participants—when they reach the completion of their treatments. A proportion (20/100, 20%) of all ulcer photographs will be measured by 2 assessors to estimate interrater reliability. These photographs will be selected at random.

Treatment will stop when the local clinician determines that complete epithelization has taken place. Photographs will be taken at this point and at the follow-up visit.

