#### Data Management

All data generated from this study will be classified according to the University of Birmingham Information Security Framework. All data will be collected and stored electronically to reduce data entry errors, such as contradicting answers. Data will be reported on an electronic case report form, and all local staff will be trained to collect data directly onto electronic tablets. Data will be acquired and stored on the REDCap database platform, with access restricted by passwords at both the University of Ibadan and the local site in Nigeria. Each participant will be allocated a unique study number when they agree to participate (and before randomization), which will be used on all documents. A master list linking a trial participant number to their identity (name) will be retained by the hospital securely in a locked filing cabinet. This is necessary so that the notes of any person who withdraws consent for data storage can be removed. The trial participant master list will be stored separately from patient lists and the trial data.

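### The date and trial number on the in-frame ruler let assessors link and date-order a participant's photographs, which weakens the shuffling and lets one residue-bearing image expose others

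*Protocol article*

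**What the plan says.** Under Plans for the Assessment and Collection of Outcomes, the protocol article sets out the photograph workflow step by step. Photographs are taken twice weekly. For calibration, the frame includes "a 3-cm clean paper ruler with the date and participant’s trial identification number". The images are uploaded to REDCap and accessed by the database managers. The next step is: "The ulcer photos will then be randomized and sent to the blinded assessors in Nepal for the measurement of ulcer dimensions". The observer then traces the ulcer by hand with a mouse, and software computes the area.

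The same section says "The assessors will be blinded to the treatment allocated to the participant", and on distribution: "All photographs from a given participant will be assigned to the observers at random". On timing, "they will be made in batches of 10 participants—when they reach the completion of their treatments". Twenty percent of photographs are read by two assessors, and residual honey is to be removed with a wet swab before the photograph.

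The section on the interval pilot states the concern that observers may be able to see honey residue. If they can, it considers alternating dressings and weekly observation.

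The article describes the timing of the study number in two ways. Data Management says: "Each participant will be allocated a unique study number when they agree to participate (and before randomization". Concealment Mechanism says that, once details are submitted, "the trial arm and a unique study number will be assigned and revealed to the local clinician".

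**The concern.** Shuffling photographs before reading is useful if the reader cannot tell which images belong together or in what order they were taken. Here both facts are written on the object the reader must look at to calibrate the measurement. The text describes no step that removes them.

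Two things are at stake, and they should be kept apart.

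- **Sequence.** Manual tracing involves judgement. A reader who knows the date order may draw edges to fit an expected decline. Batches go out after treatment is complete, and treatment stops when the local clinician judges the ulcer epithelized. The last dated treatment-phase image therefore often carries that verdict too.
- **Linkage.** If one image betrays the arm through honey residue, a visible participant number carries that knowledge to the same participant's other images.

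The areas feed the rate-of-healing model, whose treatment effect is the time-by-treatment interaction. Participants and dressing staff know the arm, so blinded reading of photographs is the main protection for this outcome.

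**Working it through.** The plan gives no figure to reproduce. The check is a reading of the workflow, followed by an illustration.

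**Reading the workflow**

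1. The frame contains the date and the trial number (Plans for the Assessment and Collection of Outcomes).
2. The number is constant for each participant and is used on all documents (Data Management). It is also linked to the photographs (the section on additional consent provisions).
3. Between upload and reading, the only step described is randomization.
4. The ruler is the scale, so it has to stay visible.
5. It follows that a shuffled batch of 10 participants can be sorted by participant and date from the labels alone.
6. The wet swab and the pilot's fallback act on how often residue is seen. Neither breaks the link between images.

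**How far one revealing image reaches**

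- If one observer reads all of a participant's photographs, it reaches the whole series.
- If photographs are assigned singly, assume three observers (the pilot uses three; the article gives no number for the main reading). With 20% double reading, each observer reads 0.8 × 1/3 + 0.2 × 2/3 = 0.267 + 0.133 = 0.40 of the series.

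The sentence on random assignment to observers does not settle which of these applies.

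**Chance of at least one revealing image**

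The documents give no residue rate. Assume p = 2% to 5% per honey-arm image after swabbing, independent between images. The chance is 1 − (1 − p)^n.

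- Full series: 2 per week × 12 weeks gives n = 24.
- Typical series: with 90% healed by day 84 (the sample-size assumption for honey) and a constant hazard, the hazard is −ln(0.1)/84 = 0.0274 per day. The median is ln 2/0.0274 ≈ 25 days, or about 7 images.

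| Images | p = 2% | p = 5% |
|---|---|---|
| 7 | 1 − 0.98^7 = 13% | 1 − 0.95^7 = 30% |
| 24 | 1 − 0.98^24 = 38% | 1 − 0.95^24 = 71% |

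With unlinked images, a revealing image exposes only its own reading, that is 2-5% of honey-arm readings.

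The 24-image row applies to few honey-arm participants: 10% are unhealed at day 84 under the same assumption. If images are split as above, one observer sees about 10 of the 24 (0.40 × 24 = 9.6). The chance that this observer meets a revealing image is then 1 − 0.98^10 = 18% to 1 − 0.95^10 = 40%.

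Residue probably clusters within participants, for example through wound shape or the person dressing the wound. Positive clustering lowers every figure in the table.

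**The case against.** The strongest reply is that a journal article need not describe image handling in full, and that the central step may already crop or recode the labels. That is possible, and it limits the point to the workflow as written. It does not remove the point. The article lists the steps, states what is in the frame, and names randomization as the only action before reading. A site following this text would send labelled images.

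Other objections stand and set the bounds of the point.

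- A reader might infer that the labels themselves unblind the assessors. They do not. Nothing says that the number encodes the arm, and an arm-revealing image is needed first.
- A reader might infer that one such image always exposes the whole series. The article assigns a participant's photographs to observers at random, so the exposure may stop at the share one observer reads.
- A reader might infer that the shuffling achieves nothing. It still removes the default chronological presentation.
- The article promises blinding to treatment, not to sequence. Anchoring from date order acts in both arms and does not by itself favour one.
- The swab and the pilot should lower the residue rate, which drives the whole illustration.

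It is also tempting to say that only the rate-of-healing outcome depends on blinded reading. The article does not establish this, because its abstract says that blinded observers determine the outcomes, in the plural.

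**Conclusion.** The point holds as a weakness in the stated workflow. With date and number readable in the frame and no masking described, assessors can link and order images. This works against the shuffling and can anchor manual tracing. The differential risk is conditional on visible residue, which the protocol itself treats as a concern. One such image then exposes all of that participant's images read by the same assessor: the full series under single-observer reading, or about 40% under the three-observer assumption.

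The ranges of 13-30% and 38-71% are illustrations. They rest on an assumed 2-5% residue rate and on independence between images, and neither comes from the documents. No direction or size of bias in the treatment effect can be derived from the article. The defect does not depend on these percentages.

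The two statements on when the study number is issued conflict. This has no bearing on linkage and carries only minor weight.

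**What to change.** State in the photograph workflow that, before distribution, the database managers mask or crop the date and trial number, leave the 3-cm scale visible, and give each image a random code. The managers hold the key linking code to participant and date. They already access the photographs, and the Researcher Blinding section lists them among those who know the allocation, so holding the key unblinds nobody new. If masking is already done, one sentence saying so is enough. State also whether photographs are assigned to observers singly or by participant.

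The cost is a modest central task: at most about 130 × 24 = 3,120 treatment-phase images, with care that the scale stays readable. It needs no extra visits or participants. Because recruitment has begun, the step can apply only to images not yet read, or to images that are re-read.

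Separately, reconcile Concealment Mechanism with Data Management on when the study number is issued.
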